## Abstract

**Background:**

Physical activity prevents or delays progression of impaired glucose tolerance in high-risk individuals. Physical activity promotion should serve as a basis in diabetes care. It is necessary to develop and evaluate health-promoting methods that are feasible as well as cost-effective within diabetes care. The aim of Sophia Step Study is to evaluate the impact of a multi-component and a single component physical activity intervention aiming at improving HbA_1c_ (primary outcome) and other metabolic and cardiovascular risk factors, physical activity levels and overall health in patients with pre- and type 2 diabetes.

**Methods/design:**

Sophia Step Study is a randomized controlled trial and participants are randomly assigned to either a multi-component intervention group (A), a pedometer group (B) or a control group (C). In total, 310 patients will be included and followed for 24 months. Group A participants are offered pedometers and a website to register steps, physical activity on prescription with yearly follow-ups, motivational interviewing (10 occasions) and group consultations (including walks, 12 occasions). Group B participants are offered pedometers and a website to register steps. Group C are offered usual care. The theoretical framework underpinning the interventions is the Health Belief Model, the Stages of Change Model, and the Social Cognitive Theory. Both the multi-component intervention (group A) and the pedometer intervention (group B) are using several techniques for behavior change such as self-monitoring, goal setting, feedback and relapse prevention.

Measurements are made at week 0, 8, 12, 16, month 6, 9, 12, 18 and 24, including metabolic and cardiovascular biomarkers (HbA_1c_ as primary health outcome), accelerometry and daily steps. Furthermore, questionnaires were used to evaluate dietary intake, physical activity, perceived ability to perform physical activity, perceived support for being active, quality of life, anxiety, depression, well-being, perceived treatment, perceived stress and diabetes self- efficacy.

**Discussion:**

This study will show if a multi-component intervention using pedometers with group- and individual consultations is more effective than a single- component intervention using pedometers alone, in increasing physical activity and improving HbA_1c_, other metabolic and cardiovascular risk factors, physical activity levels and overall health in patients with pre- and type 2 diabetes.

**Trial registration:**

ClinicalTrials.gov Identifier: NCT02374788. Registered 28 January 2015.

## Background

Having type 2 diabetes, but also pre-diabetes increases the risk of cardiovascular disease (CVD) and premature death [1]. Physical activity on a regular basis enhances metabolic control [2, 3], improves blood lipid profile, blood pressure and quality of life [2, 4]. Several studies have shown preventive effects of physical activity in individuals with impaired glucose tolerance [5–9] and physical activity in persons with type 2 diabetes clearly lowers the risk of cardiovascular disease and premature death [10, 11]

The recently updated Swedish recommendations for physical activity for persons with type 2 diabetes are in line with the US PA Guidelines recommendation of 2008 [12, 13]. The recommendations are “To undertake at least 150 min per week of moderate to vigorous intensity aerobic physical activity spread out during at least 3 days during the week with no more than two consecutive days between the bouts and moderate to vigorous resistance training at least 2-3 days per week [2, 12]. There is a dose–response relationship between aerobic physical activity and health gains, and activity duration beyond 150 min per week is associated with an even greater decline in HbA_1c_ [14] as well as a reduced risk of cardiovascular disease and all-cause mortality in patients with diabetes [10]. An increased body of evidence is pointing at the importance of resistance training or combined training for blood glucose control [2, 3, 15] and a high relative muscle mass for better insulin sensitivity [16]. It is also evident that reducing sedentary time and breaking up sitting time may give additional health benefits over the recommended activities and might be of importance especially for the most inactive and unfit individuals [2, 17, 18]. The most important component to maintain these beneficial effects seems to be continuous repetition and it is therefore crucial that physical activity is perceived as enjoyable and that it is incorporated in daily routines [2]. In the Swedish population, 52 % of adults are regarded as being sufficiently active [19] and self-reported data from the Swedish National Diabetes Register showed that in the population with diabetes 55 % reached 3 × 30 min per week [11]. It is considered crucial to find and evaluate strategies to increase the adoption and maintenance of regular physical activity in the population with pre-and type 2 diabetes [2, 11].

Advising physical activity is both cost-effective and feasible in primary care [20, 21] and promotion of physical activity should serve as a basis in diabetes care [1, 22]. The Board of Health and Welfare (Socialstyrelsen) in Sweden gives high priority to physical activity in diabetes care and since 1999 strongly recommends primary care to provide advice and support for individuals with diabetes as well as for individuals with increased risk for developing diabetes [23, 24]. Given the low number of people with diabetes being sufficiently active, the promotion of physical activity in the Swedish diabetes care is not satisfactorily effective today and needs to be improved [25].

In the literature, a number of methods reinforcing physical activity promotion in primary care have been evaluated and shown to be effective. The World Health Organization put emphasis on primary care to encourage and support people to take better care of their own health and to use evaluated tools and technology for this purpose [26]. Pedometers have been helpful in increasing physical activity levels and in improving metabolic parameters in patients with diabetes in several previous studies [27–29]. Pedometers have also been efficient in increasing the number of steps with a subsequent improvement in blood pressure even in already healthy individuals [30]. An advantage with pedometers is their efficiency in increasing the motivation to be more active and less sedentary on a daily basis, which is especially important for metabolic control and in lowering blood pressure. Well-planned group counseling sessions led by health professionals have also been shown to be effective in reducing diabetes risk in several previous interventions [28, 31–33]. The group setting offers social support and a pronounced opportunity for participants to share experiences, encouragement and to strengthen change. Group education is emphasized in the Swedish diabetes care [23, 24] but is today used by only 24 % of primary care units [25].

Recent reviews on physical activity interventions in primary care demonstrate that exercise prescription is a successful method to increase physical activity up to 12 months [21, 34]. In the Swedish primary care, a treatment method named FaR® (abbreviation for Physical Activity on Prescription) is recommended for use in a number of diseases including type 2 diabetes [35]. The focus is on person-centered counseling and the current diagnosis, health status, history of physical activity, risks and preferences of the individual serves as a basis for the counseling. FaR is based on Social Cognitive Theory and the Stages of Change Model. In an evaluation 2010 87 % of the Swedish health care centers had implemented FaR [36].

Motivational Interviewing is a counseling method using a person-centered approach [37]. There is some inconsistency in the evidence for motivational interviewing both in diabetes care and in increasing physical activity in the primary care setting: unfortunately many studies fail to pick up treatment fidelity, the qualification of the professionals delivering the treatment, mode of delivery and intervention intensity [38, 39]. Alongside with other intervention components, such as self-monitoring, physical activity on prescription and offering more than two motivational interviewing sessions the efficacy may be improved [39]. In the promotion of physical activity flexibility using various approaches is recommended [40–42] as well as to tailor the intervention to the individual [43].

There is still a gap in the evidence on which methods, what intervention components and what support intensity would be most effective in increasing long-term physical activity in in the primary care setting for persons with pre- and type 2 diabetes [21, 43, 44]. More evidence is also needed on maintenance strategies for long-term effectiveness [33, 44].

Based on these identified gaps in knowledge, Sophia Step Study has been developed as an evidence-based structured, two-year health promotion program at two intensity levels of support focusing on physical activity and aimed for the primary care setting. The study aims to evaluate and explore the impact of two levels of intervention intensities of physical activity support on health parameters.

The aim of this paper is to describe the design and recruitment procedure, methods, and the theoretical framework for the physical activity promotion program Sophia Step Study.

## Methods/design

### Main objective

The main objective of Sophia Step Study is to evaluate the impact of a multi- component and a single-component primary care physical activity intervention aiming at improving HbA_1c_ (primary outcome) and other metabolic and cardiovascular risk factors, physical activity levels and overall health in patients with pre-diabetes and type 2 diabetes.

### Hypothesis

The hypothesis is that both levels of intervention have effect on the primary outcome HbA_1c_, with the multi-component intervention having superior and longer lasting effects.

### Study design and recruitment

The Sophia Step Study is a two-year randomized controlled trial (RCT) with three parallel groups. The CONSORT statement is followed [45]. The study takes place at the primary health care centers at Sophiahemmet, Stockholm, Sweden.

All patients at the health care centers diagnosed with pre-diabetes and type 2 diabetes and fulfilling the inclusion criteria are informed of the study and asked whether they are interested in participating (Fig. 1). Patients showing interest receive a letter with further information and are subsequently interviewed over telephone by the diabetes specialist nurse and asked a set of inclusion/exclusion questions. If they fulfil the inclusion criteria they are booked for a baseline control.

**Fig. 1 Fig1:**
[figure not shown]
Recruitment procedure and randomization of Sophia Step Study subjects

#### Inclusion criteria

Age 40-80 years and ability to communicate in Swedish. Either Pre-diabetes (HbA_1c_ > 39- < 47 mmol/mol and/or fasting glucose >5.6 mmol/l) or diagnosed with type 2 diabetes with a duration of ≥1 year.

#### Exclusion criteria

Myocardial infarction in the past 6 months, serum creatinine >140 mmol/l, diabetic foot ulcer or risk of ulcer (severe peripheral neuropathy), on insulin since the last 6 months, additional disease prohibiting physical activity, repeated hypoglycemia or severe hypoglycemia in the past 12 months, being very physically active according to the Stanford Brief Activity Survey [46] or having no access to internet.

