### Procedure and timeline

The baseline measurements start with an examination by the patient’s general practitioner for exclusion purposes. A notification is made on subjects not fulfilling the criteria at this stage. The study-specific measurements are made by the diabetes specialist nurse or a trained assistant, followed by randomization to three groups using closed envelopes while stratified by gender. The participants are randomly assigned to either the multi-component intervention group (A), the single component group (B) or a control group (C). A total of 310 patients with pre- diabetes or type 2 diabetes will be included gradually, with the aim of 100 participants included in group A and B, and 110 in the control group C by the end of 2017. After randomization, participants are given a schedule for measurement time points and group A participants receive a schedule for group sessions and individual consultations. The intervention lasts for 24 months, with more intensive support from the health care professionals within the first 24 weeks, and less support in the second year (Fig. 2).

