**Biomarkers**									
HbA_1c_ (mmol/mol)	✓		✓		✓		✓		✓
Plasmaglucose (fasting) mmol/l	✓		✓		✓		✓		✓
Triglycerides (mmol/l)	✓		✓		✓		✓		✓
LDL (mmol/l)	✓		✓		✓		✓		✓
HDL (mmol/l)	✓		✓		✓		✓		✓
Total Cholesterol (mmol/l)	✓		✓		✓		✓		✓
Free fatty acids (mmol/l)	✓		✓		✓		✓		✓
Insulin (mU/l)	✓		✓		✓		✓		✓
IGF BP1 (μ/l)	✓		✓		✓		✓		✓
ApoA1 (g/l)	✓		✓		✓		✓		✓
ApoB (g/l	✓		✓		✓		✓		✓
C-peptid (pmol/l)	✓		✓		✓		✓		✓

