#### Biomarkers

Measurements include fasting blood samples on HbA_1c_ (mmol/mol), plasma glucose (mmol/l), triglycerides (mmol/l), LDL (mmol/l), HDL (mmol/), total Cholesterol (mmol/l), free fatty acids (mmol/l), Insulin (mU/l), IGF BP1 (μ/l), Apolipoprotein-A1 (g/l), Apolipoprotein B (g/l) and C-peptid (nmol/l). HbA1c, haemoglobin A1c (ref < 5.2 %) is determined with immunologic MonoS method, Unimate (Roche Diagnostics, Basel, Schweiz). To convert HbA1c MonoS into HbA1c (DCCT) NGSP (National Glycoprotein Standardization Programme) the formula, NGSP = 0.92*MonoS + 1,33 is used. Plasma glucose are determinedwith a glucose oxidase method, total Cholesterol and triglycerides are determined by using enzymatic method, LDL and HDL are determined by using a homogeneous method, Apolipoprotein-A1 and Apolipoprotein B are determined by using turbimetric method and C-peptid are determined by using immunometric method using two monoclonal antibodies and detection with electrochemiluminiscense using a Modular E system (Beckman Coulter, Inc.). Serum insulin concentrations are determined with RIA-kits purchased from Pharmacia & Upjohn, Stockholm. IGFBP-1 concentrations in serum are determined by RIA according to the method of Póvoa et al. [50]. Samples are saved for later free fatty acid analyses.

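### The creatinine exclusion is printed in a unit that leaves it empty, and the fasting-glucose limb of pre-diabetes has no upper bound

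*Protocol article*

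**What the plan says.** The Exclusion criteria section of the protocol article lists "serum creatinine >140 mmol/l". It is the only creatinine limit in the document, and no reason for it is given.

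The Inclusion criteria section offers two routes. The first is "Either Pre-diabetes (HbA_1c_ > 39- < 47 mmol/mol and/or fasting glucose >5.6 mmol/l", with the figures in brackets after the label. The second is "diagnosed with type 2 diabetes with a duration of ≥1 year".

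Study design and recruitment says that those "diagnosed with pre-diabetes and type 2 diabetes and fulfilling the inclusion criteria are informed of the study", so the patients approached already carry one of the two diagnoses. A telephone interview with inclusion and exclusion questions follows. Procedure and timeline then adds: "The baseline measurements start with an examination by the patient’s general practitioner for exclusion purposes".

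**The concern.** An eligibility limit has to be usable as written, because readers and screening staff take the trial population from it. A creatinine limit that nobody can exceed does no work.

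The inclusion rule raises a smaller difficulty. HbA1c is bounded on both sides and fasting glucose only from below, and the and/or makes glucose sufficient alone. The type 2 branch asks for at least a year since diagnosis. The two routes can therefore pull against each other: someone with HbA1c above the pre-diabetes range and no year-long diagnosis may fail the second route yet satisfy the figures of the first.

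At stake is a clear description of who was studied. HbA1c is the primary outcome and also the variable left without a ceiling on this route. The Limitations section already doubts that pre-diabetes and diabetes will show the same HbA1c decline. Randomization is stratified by gender only, so diabetes status is not balanced by design. The diabetes distress questionnaire (Swe-PAID-20) is answered only by participants diagnosed with diabetes, so the label also decides what is collected.

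**Working it through.** The plan has no figure of its own to reproduce here. Two checks apply.

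**1. Creatinine unit**

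Inputs: the printed limit, 140 mmol/l (Exclusion criteria); molar mass of creatinine, 113.12 g/mol (a physical constant, not in the document).

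Formula: mass concentration = molar concentration × molar mass.

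- As printed: 0.140 mol/l × 113.12 g/mol = 15.8 g/l, or about 1,584 mg/dl.
- Same number in micromol/l: 0.000140 mol/l × 113.12 g/mol = 0.0158 g/l, or about 1.6 mg/dl.
- Ratio: 15.8 / 0.0158 = 1000.

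The second line only shows the size of the mismatch; it does not say which limit was meant. That no patient could have 15.8 g/l rests on general physiology, not on the document.

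Units also disagree elsewhere. Table 1 gives "C-peptid (pmol/l" and the Biomarkers text gives "C-peptid (nmol/l", again a factor of 1000. This makes a typing error more likely but does not recover the intended creatinine limit.

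**2. The inclusion rule as printed**

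With H = HbA1c (mmol/mol), G = fasting glucose (mmol/l) and D = years since a type 2 diagnosis, the literal rule is:

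eligible = (39 < H < 47 or G > 5.6) or (diagnosed type 2 diabetes and D ≥ 1)

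The profiles below are illustrative. The last column keeps the same figures but reserves the pre-diabetes route for people with no type 2 diagnosis.

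| H | G | Type 2 diagnosis | Literal rule | Label respected |
|---|---|---|---|---|
| 42 | 5.0 | none | eligible | eligible |
| 55 | 8.5 | none | eligible | eligible |
| 55 | 8.5 | 0.25 year | eligible | not eligible |
| 80 | 14 | 0.1 year | eligible | not eligible |
| 55 | 5.2 | 0.25 year | not eligible | not eligible |
| 55 | 8.5 | 2 years | eligible | eligible |

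Row 2 is the gap that survives either reading: HbA1c above the pre-diabetes range, no diagnosis, and entry on glucose alone. Rows 3 and 4 are admitted only if the bracketed figures override the label. Row 5 shows that the 1-year rule still acts on the literal reading: it keeps out recent-onset patients whose fasting glucose is 5.6 or below and whose HbA1c is outside the range. Nothing in the Exclusion criteria caps HbA1c or glucose, or removes diabetes of under one year.

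**The case against.** On creatinine, the best reply is that this is a typing slip in an article. A general practitioner checks exclusions and would hardly apply an impossible number literally; the working protocol and screening form are not shown and may be correct. That stands as far as practice goes. A reader might infer that the renal exclusion failed in the trial and that unsuitable patients were enrolled; the document does not show that. It does not remove the defect in the published criterion, which cannot be recovered from the text.

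On glucose, the reply is stronger. The figures qualify the label of pre-diabetes, diagnosed type 2 diabetes has its own route, and the patients approached already carry a diagnosis. A clinician would not ordinarily file a patient diagnosed last month as pre-diabetes. A reader might infer that the 1-year rule has no effect, or that everyone with diabetes of under a year and glucose above 5.6 mmol/l qualifies. Neither follows: the label and sentence structure speak against it, and the rule still excludes some patients even when read literally. What remains is mainly diabetes-range HbA1c that is not yet diagnosed.

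It is also fair to say that harm to the primary outcome is not shown. Such patients would be randomized across all three groups, so the expected effect is added heterogeneity, not bias between groups. The article plans no analysis by diabetes status that mislabelling would damage.

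**Conclusion.** The creatinine point holds without reservation on the printed text: the limit is about 1000 times the same number in micromol/l, excludes nobody as written, and is corrected nowhere. It assumes only the molar mass and the physiological impossibility of 15.8 g/l. A misprint is the probable explanation, and its reach into actual screening is unknown.

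The glucose point holds as a secondary matter. The pre-diabetes definition is open at the top on one limb, so people with HbA1c of 47 or above, chiefly those not yet diagnosed, could enter under that label without meeting the 1-year rule. How many did cannot be told from the document.

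Both affect who is studied and how reproducible that population is. The sample-size calculation uses an assumed difference and standard deviation drawn from earlier literature, and neither eligibility limit enters it, so no sample-size or power figure changes. The correction should be made, mainly because the creatinine error is certain and cheap to resolve.

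**What to change.** - **Creatinine.** Reconcile the number and unit with the approved protocol and the laboratory's reporting unit, then correct the published criterion. Confirm from the screening form which limit was applied to patients already screened. If the form carries the misprint, correct it for the remaining recruitment, which is planned to the end of 2017.
- **Inclusion branches.** Reconcile the pre-diabetes and type 2 routes so that they do not conflict, and state how a person with HbA1c outside the pre-diabetes range and no year-long diagnosis is handled. The sponsor must settle any bound from the approved protocol; none is proposed here.
- **Participants already enrolled.** List those who entered on fasting glucose alone, with baseline HbA1c and diagnosis status, so that the size of the gap is known and can be reported.

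The cost is a correction notice, a check of the screening records and one listing. If the reconciled rule is narrower than the printed one, slightly fewer patients will be eligible.

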### Procedure and timeline

The baseline measurements start with an examination by the patient’s general practitioner for exclusion purposes. A notification is made on subjects not fulfilling the criteria at this stage. The study-specific measurements are made by the diabetes specialist nurse or a trained assistant, followed by randomization to three groups using closed envelopes while stratified by gender. The participants are randomly assigned to either the multi-component intervention group (A), the single component group (B) or a control group (C). A total of 310 patients with pre- diabetes or type 2 diabetes will be included gradually, with the aim of 100 participants included in group A and B, and 110 in the control group C by the end of 2017. After randomization, participants are given a schedule for measurement time points and group A participants receive a schedule for group sessions and individual consultations. The intervention lasts for 24 months, with more intensive support from the health care professionals within the first 24 weeks, and less support in the second year (Fig. 2).

**Fig. 2 Fig2:**
[figure not shown]
Time frame for Sophia Step Study. Time points for intervention components (grey) and data collection (black) for all groups. *Including blood samples, anthropometric and physical activity measurements and questionnaires. More details are depicted in Table 1

Sophia Step Study started with a pilot group in March 2013, entailing 8 participants in group A and 6 in group C. The pilot revealed compliance to the protocol and ability to recruit and the first participants were recruited in November 2013. The plan is to have 310 participants completed the intervention in 2020.

